#### 8.6 Aim 5: Composite outcome

We will build this model using the CS population with follow-up, and the outcome will be a composite of SSI, maternal mortality, or neonatal mortality within 30 days. Otherwise, the model features and interpretation will be the same as the primary model. Since SSIs are more common than maternal or neonatal deaths, we expect the results of this model may be similar to the primary model.

#### 8.7 Aim 6: Relate compliance to SSIs

Our overall theory of change is that the intervention will cause higher compliance with proven infection prevention behaviors, which will in turn cause a reduction in SSIs. In other words, if the intervention proves effective, then we would expect it to work through the mechanism of raising compliance scores. We will test this theory by swapping out the intervention indicator variable for the indicator of a high-compliance operation.

Then, using the CS population with follow-up, we will build the same model as our primary analysis except to drop intervention status and replace it with the high compliance binary variable. This will become the predictor of interest for this aim only.

We will interpret this OR in light of the results on aim 1. That is, if the intervention is effective, then we expect that the “intervention phase” binary variable and the “high compliance operation” binary variable will capture highly overlapping cases. In fact, the more successful the intervention, the more strongly these two variables will be correlated. If the intervention succeeds in aim 1 then we will expect the OR for high compliance in this model to be of the same direction ( $<1$ ) and roughly comparable in significance.

If the intervention does not succeed in aim 1, then this model will function like an assay sensitivity test. The infection reduction activities in Clean Cut are extraordinarily well established in the clinical and public health literature. If we find that higher compliance operations are *not* associated with SSI rates, that will cast doubt on all the trial results and pose larger questions about measurement, data quality, and our implementation strategy in this trial.

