### 1.2. Multiple comparisons

This analysis includes 6 aims, which collectively involve fitting 12 models (Table 7). Each model has a single predictor of interest, which is the intervention variable in all models except in aim 6, where the predictor of interest is the flag for high-compliance surgeries. We will evaluate each p value against an alpha of 0.05 and will not adjust for multiplicity.

Table 7: Number of planned models across all aims

|            |       |                                                | N models |
|------------|-------|------------------------------------------------|----------|
| Primary    | Aim 1 | Infection reduction in CS                      | 1        |
| Secondary  | Aim 2 | 6 compliance domains, 1 overall score          | 7        |
|            | Aim 3 | Reduced maternal postoperative mortality       | 1        |
|            | Aim 4 | Reduced neonatal mortality                     | 1        |
| Additional | Aim 5 | SSI, maternal mortality, or neonatal mortality | 1        |
|            | Aim 6 | Compliance, surgical infection                 | 1        |

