### 8.3 Aim 2: Improved compliance with infection prevention practices

Using the total intraoperative population, we will report percentages of compliance for each of the six key areas of infection prevention in the control and intervention groups. Then, we will construct six models using each binary in turn as the dependent variable, and dropping the vector of demographic variables, which are not likely to be causally related to compliance. If the estimated OR of a behavior being performed under the intervention is greater than 1 and statistically significant, then we will conclude a positive effect of the intervention on that behavior. Finally, we will fit a last model using “high compliance” (defined as a compliance score of >4) as the outcome.

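### Aim 6 is presented as a test that Clean Cut lowers SSI by raising compliance, but its model omits the intervention and is read with Aim 1 only; a mechanism statement should also require the Aim 2 result

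*Combined protocol and SAP*

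**What the plan says.** SAP section 8.7 gives the theory of change as "the intervention will cause higher compliance with proven infection prevention behaviors, which will in turn cause a reduction in SSIs". On how it will be examined, the section says: "We will test this theory by swapping out the intervention indicator variable for the indicator of a high-compliance operation". The model is the primary model of section 7.1 (18 month categories, a random cohort effect, the fixed controls), altered to "drop intervention status and replace it with the high compliance binary variable". The multiple-comparisons subsection (numbered 1.2 in the SAP body) says the same of Aim 6, "where the predictor of interest is the flag for high-compliance surgeries".

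The reading rule is "We will interpret this OR in light of the results on aim 1". It has two branches:

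- If Aim 1 succeeds, the compliance odds ratio is expected to be "of the same direction", that is below 1, and of about the same significance. The reason given is that "the more successful the intervention, the more strongly these two variables will be correlated".
- If Aim 1 does not succeed, the model serves as an assay sensitivity check.

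The effect of the intervention on compliance is modelled in section 8.3 (Aim 2). After the six domain models, that section says "Finally, we will fit a last model using" the high-compliance flag as outcome. Section 8.7 does not refer to this result, and no indirect-effect analysis is planned.

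**The concern.** The theory needs both links. A model without the intervention can bear on the second link but carries no test of the first. Operations differ in compliance within the same cohort and period whether or not Clean Cut changed anything, and the SAP itself regards the practices as firmly established. An odds ratio below 1 is therefore likely in any case.

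Aim 1 does not fill the gap, because it estimates the total effect on SSI by whatever route. A positive Aim 1 with a protective compliance flag is the pattern section 8.7 expects from a working mechanism. The same pattern arises when the intervention lowers SSI by some other route and leaves compliance where it was. At stake is what the paper may say about how Clean Cut works, which matters to hospitals deciding which parts to adopt.

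**Working it through.** **1. Which link each model addresses**

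| Analysis | Outcome | Predictor of interest | Population (SAP section 6) | What it bears on |
|---|---|---|---|---|
| Aim 1 (8.2) | SSI | intervention | CS with auditor follow-up | total effect |
| Aim 2, last model (8.3) | high compliance | intervention | all operations with intraoperative data | first link |
| Aim 6 (8.7) | SSI | high compliance; no intervention term | CS with auditor follow-up | second link |

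Section 8.7 combines the first and third rows. The second row is needed and is not used.

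**2. Figures in the plan.** The SAP gives no power or effect size for Aim 6, so there is nothing to reproduce beyond the Table 7 tally: 1+7+1+1+1+1 = 12 models, as stated.

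**3. How readily Aim 6 is significant if Clean Cut leaves compliance unchanged**

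Inputs:
- about half of operations highly compliant (SAP, measurement of compliance);
- SSI of 9-12% in low-compliance operations (assumed from the control range in SAP 4.2);
- two-sided alpha of 0.05 (two-sided assumed);
- N from 2,800 (assumed) to 5,525 (Table 3), because the number of CS patients with auditor follow-up is not given.

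Power ≈ Φ(|p1−p2|/SE − 1.96), with SE = √{[p1(1−p1)+p2(1−p2)]/(N/2)}.

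Example with N = 5,525, p1 = 0.09 and relative risk 0.65:
- p2 = 0.0585
- SE = √[(0.0819+0.0551)/2,762.5] = 0.00704
- z = 0.0315/0.00704 = 4.47
- power = Φ(2.51) = 99.4%

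| Relative risk, high vs low compliance | N = 5,525 | N = 2,800 |
|---|---|---|
| 0.54 | over 99% | 99.1-99.9% |
| 0.65 | 99.4-99.9% | 88.9-96.1% |
| 0.80 | 69-82% | 42-53% |

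The pilot's 0.54 (protocol, Program Evidence) compares scores 3-6 with 0-2, whereas the SAP flag is 5-6 against 0-4. It is only a guide. These figures are power for a true association.

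**4. Simulation of the reading rule.** There were 250 trials per scenario on the auditor counts of Table 4 (2,764 control + 2,828 intervention = 5,592), with 5 cohorts and 18 months. SSI was about 10% and the cohort SD 0.2 on the logit scale. Cohort was fitted as a fixed effect and patient controls were omitted. Each entry is the share significant in the favourable direction.

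| High compliance, control → intervention | Compliance OR | Direct intervention OR | Aim 1 | Aim 2 | Aim 6 | Aims 1 and 6 |
|---|---|---|---|---|---|---|
| 50% → 50% | 0.50 | 1.00 | 2.4% | 2.8% | 100% | 2.4% |
| 50% → 50% | 0.65 | 1.00 | 2.0% | 2.0% | 100% | 2.0% |
| 50% → 50% | 0.50 | 0.55 | 76.4% | 0.8% | 100% | 76.4% |
| 30% → 70% | 1.00 | 0.55 | 74.4% | 100% | 9.6% | 7.6% |

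The third row is the problem case. Its Monte Carlo standard error is √(0.764×0.236/250) = 2.7 percentage points. In the fourth row compliance rises but is inert. Aim 6 is significant in 9.6%, against 4.8% with the intervention kept in, because the flag partly stands in for the omitted term.

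**5. A weaker direct effect.** A second simulation (400 trials per scenario, Table 3 counts and 80% of them, 12% control SSI) gave a standard error for the Aim 1 log OR of 0.18-0.22. At a direct OR of 0.725, |ln 0.725| = 0.322, so Aim 1 power is:
- Φ(0.322/0.18 − 1.96) = Φ(−0.17) = 43%
- Φ(0.322/0.22 − 1.96) = Φ(−0.50) = 31%

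Aims 1 and 6 cannot both be positive more often than this.

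**6. Similar significance.** In the second simulation the Aim 6 log OR had a standard error of about 0.09-0.10, roughly half that of Aim 1. Equal odds ratios would therefore give z statistics about twofold apart.

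**7. Effect of adding conditions.** In the first three rows of step 4, keeping the intervention in the Aim 6 model left the compliance flag significant in 100% of trials, so that step alone cures nothing. Requiring the first link as well caps the rate at the Aim 2 column, 0.8-2.8%. In the second simulation the joint rule was met in 1-4% of trials with compliance unaffected. It was met in 82-100% when Clean Cut raised compliance from 35% to 65% and acted only through it.

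**The case against.** The other side has good points, and most of them stand.

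- Aim 6 is titled and introduced as relating compliance to SSI, and Table 5 lists it as additional and not pre-specified. Sections 8.2 and 8.3 say when an effect will be concluded; section 8.7 says only what is expected. This stands: the SAP does not commit itself to declaring the mechanism proven.
- Aim 2 tests the first link and belongs to the same analysis, so a null Aim 2 would be visible beside Aim 6. This also stands. The gap is that section 8.7 never makes its reading depend on it.
- If Aim 1 fails, Aim 6 becomes an assay sensitivity check. This removes the scenarios with no SSI effect, where Aims 1 and 6 were both positive in only 2.0-2.4% of trials.

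Three stronger readings are tempting, and the documents do not support them:

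- A reader might take the near-100% rates for Aim 6 as a false-positive rate. In those scenarios compliant operations truly have fewer infections, so rejecting the fitted model's null is correct. The SAP states no other null for this aim.
- A reader might argue that the two flags cannot overlap much, because only 0.052 of 0.250 (21%) of the intervention term's variance remains after month and cohort. Section 8.7 speaks of raw overlap between cases, which residual variance does not address.
- A reader might call mechanism a main aim of the paper. Table 5 says otherwise.

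**Conclusion.** The point holds in a limited form. Section 8.7 describes as a test of a two-link theory a model that informs one link, and it reads the result against the total effect rather than against the missing link. The problem is confined to a positive Aim 1. There the expected pattern can arise without mediation in about 76% of trials at a direct OR of 0.55, and in at most about 31-43% at 0.725.

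These sizes rest on assumed effects, on compliance being protective regardless of Clean Cut, on cohort as a fixed effect, and on follow-up totals that appear to include operations other than CS. Table 3's arm counts sum to 5,592 against its N of 5,525, which does not affect the conclusion. That the Aim 6 model contains no test of the first link needs none of these assumptions. The primary analysis and its result are untouched.

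**What to change.** In section 8.7:

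1. Describe Aim 6 as an observational association between high compliance and SSI, and drop the claim that it tests the theory of change.
2. Allow a mechanism statement only if both conditions hold: the intervention raises high compliance (the Aim 2 high-compliance model, repeated in the CS population with follow-up), and the flag remains associated with lower SSI with the intervention kept in the model.
3. State that compliance is not randomised and that its association with SSI may be confounded.
4. Delete the expectation of similar significance for Aims 1 and 6. Keep the assay sensitivity reading for a failed Aim 1.

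A formal indirect-effect estimate is optional. If it is done, it should use one population and one covariate set. Multiplying the planned Aim 2 and Aim 6 effects would mix all operations without patient controls with followed-up CS patients with them, and a product of log odds ratios is not a clean indirect effect.

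The cost is a change of wording and two further models (Table 7 would go from 12 to 12+2 = 14), with no new data. The downside is that a mechanism statement becomes harder to reach, particularly if the Aim 2 result is weak.

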**Site randomization:** Each selected hospital will be distributed into two groups based on the type of facility: university teaching and referral hospitals in one group, and regional, district, and community hospitals in another. One hospital in each group will be paired to create five clusters; these pairings will be purposive as district and referral hospitals in Ethiopia typically have long-standing relationships which will facilitate implementation at the cluster level and prevent inadvertent crossover of the intervention prior to randomization. The sequence of implementation for each of the five clusters will be established using computer-based randomization (<https://www.randomizer.org/>).

**Participants:** As obstetric and gynecologic operations are typically undertaken in separate, dedicated operating theatres, we will focus our prospective observations on patients admitted to these theatres. Any patient undergoing surgery at any time in one of the targeted operating theatres is eligible for inclusion; there will be no exclusion criteria. Enrollment will occur at the time of observation and will include various times (day and night) and days of the week (weekdays and weekends). As the standards being implemented are not in dispute and are considered critical for ensuring antisepsis and sterility, patient informed consent will not be obtained. While our focus will be on cesarean delivery, any obstetric or gynecological operation will be included, with the inclusion of other operations in this populations (such as appendectomy for appendicitis that is found incidentally or misdiagnosed as ovarian torsion, for example). There will be no age range limit.

We will also interview key hospital personnel to understand the context of each facility, its experience with quality improvement initiatives, and the perceived importance of this work to patient safety, patient care, and the work routine. These interviewees will be recruited from the implementation teams involved in Clean Cut. We will also administer surveys in conjunction with Ariadne Labs, a partner in

this work, to understand the context, perceptions, and priorities of the various institutions, and how the Clean-CS team can support implementation at the time of intervention (phases 3, 4, and 5)

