**Figure 2: Monthly recruitment rates needed to detect selected outcome proportions**

[figure not shown]

**Analysis:** We will conduct pre/post analyses using the statistical approach recommended by Hemming with our planned assessment controlling for risk factors and other demographic and procedure variables listed below that are known to affect infection rates. We will compare patient demographics pre and post intervention as well to evaluate overall matching of patients in each part of the study. We will evaluate compliance individually and in an all-or-none manner as previously described in our Clean Cut pilot work. We will undertake a planned subanalysis of patients observed early during baseline (first two months) and compare them to patients undergoing surgery during the

final stage of the study (last two months) after implementation of the program has had time to take effect to assess primary and secondary outcomes.

As we are interested not only in the primary outcome of surgical infection but also in process improvements and the implementation strategies and support that can lead to effective compliance with best practices, we will not conduct any interim analyses. The purpose of an interim analysis is to assess the study for benefit, futility or harm. We believe that neither benefit nor futility would be readily observable at an interim analysis given the implementation strategy and approach; furthermore, even if we were able to assess benefit or futility we would want to continue the trial to fully study the mechanisms of implementation. Regarding an assessment of harm, if such an outcome were noted we believe this would most likely be due to detection bias with improving ability to capture complications as the study progressed, and we would want to let the study play out to mitigate this detection bias over time.

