## 7. General statistical considerations

### 7.1. Modeling

As stated in our protocol, we will use the statistical approach recommended by Hemming and colleagues. To estimate how the intervention is correlated with outcomes, we will fit a mixed effects logistic regression model of the form:

$$Outcome_{ij} = \beta_0 + \beta_1 Month + \beta_2 Intervention + \beta_x X + \mu_i + \varepsilon_{ij}$$

Where:

|                       |                                                                                                                                                     |
|-----------------------|-----------------------------------------------------------------------------------------------------------------------------------------------------|
| Outcome ij | Binary variable for the j th patient in the i th cohort, where 1 = had the adverse outcome, and 0 = did not have the outcome. |
| Month                 | Fixed categorical variable with 18 levels, one for each month. Reference category will be either the first or last month of the study.              |
| Intervention          | Fixed binary variable, where 1 = procedure occurred under intervention condition, 0 = procedure occurred under control condition.                   |
| X                     | Vector of fixed demographic and clinical controls                                                                                                   |
| β 0-x      | Set of regression coefficients                                                                                                                      |
| μ i        | Random effect for cohort                                                                                                                            |
| ε ij       | Error term for the j th patient in the i th cohort                                                                            |

Since this is a cross sectional design (no repeated measures on patients over time), we will not need to account for patient-level correlation over time. The random effect for cohort will account for the within-cluster variance, assuming one shared ICC. We will consider adding a random cohort-by-month interaction term, which would allow for different within-period and between-period ICCs.

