## 7.2. Controls

The protocol lists potential control variables for the analysis, but we will not be able to include them all in the model. We collected these variables because they may be clinically relevant, but they are difficult to collect in Ethiopia because medical records are poor and not every patient receives extensive prenatal care. In many cases, these clinical variables are collinear with emergency operations. Table 6 lists all the controls along with their final inclusion in the model or reason for exclusion from the model.

The final list of eight fixed controls will be: age, hypertension, gestational diabetes, rupture timing, emergency vs. elective, wound classification, ASA classification, and indication.

Table 6: Control variables

| Control variables listed in the protocol | Actual inclusion in our statistical model                               |
|------------------------------------------|-------------------------------------------------------------------------|
| Demographic                       |                                                                         |
| Age                                      | Include as categorical variable                                         |
| Gestational age                          | Drop due to poor data quality                                           |
| Gravida/parity                           | Drop due to poor data quality                                           |
| Pregnancy comorbidities                  |                                                                         |
| Hypertension                             | Include as binary                                                       |
| Pre-eclampsia                            | Drop here because it appears as one option under indication for surgery |
| Gestational diabetes                     | Include as binary                                                       |
| Obesity                                  | Drop due to low rate of obesity diagnosis in study population           |
| Malnourishment                           | Drop due to low rate of malnourishment diagnosis in study population    |
| Other comorbidities                      |                                                                         |
| HIV                                      | Drop due to low rate of HIV diagnosis in study population               |

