### 1.1. Measurement of compliance

Each of the six domains of perioperative infection prevention include two or more related behaviors. The result of each domain is measured as a binary, where 1 = all behaviors in the domain were performed during the procedure, and 0 = at least one of the behaviors was not performed.

To capture overall compliance, we will construct a “high compliance” flag where:

1 = 5 or 6 domains were performed in the surgery

0 = 0 to 4 domains were performed in the surgery

We based this cut point between 4 and 5 on the global distribution of compliance scores. This cut point roughly splits the cases: about half were high compliance, half were not.

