### 9.4 Sensitivity to choice of model

In our primary analysis (aim 1), we will use mixed effects logistic regression, fitting random intercepts for each of the five cohorts, which are defined in tables 2 and 3 above. This accounts for our hierarchical data with a random effect, so we will interpret the resulting ORs as the estimated effect of CLEAN-CUT implementation on the individual patient level (known as subject-specific or conditional estimates). An example interpretive sentence might be: “In our study, individuals who underwent a CS after CLEAN-CUT implementation were X% less likely to develop an SSI.”

In this sensitivity analysis of our primary aim, we will use a generalized estimating equation (GEE) framework with the same data. One strength of GEE is its accommodation of repeated measures of individual patients over time. While we do not measure patients repeatedly in our study, one view of our data is that the operating theater and team are measured repeatedly over time. Under this view, we will treat cohort as the unit of repeated measure in the GEE, using an autoregressive covariance structure, which assumes the strongest correlations between adjacent time periods and systematically decreasing correlations with increasing distance in time.

This accounts for our hierarchical data with repeated measures, so we will interpret the resulting ORs as the estimated effect of Clean Cut implementation on the population level (known as marginal effects). An example interpretive sentence might be: “For the hospitals in our study, the population of CS patients was X% less likely to develop an SSI after the implementation of Clean Cut.”

The difference in interpretation between ME and GEE is fairly subtle, and in most applications their estimates are similar. In the event that the magnitude or significance of the OR differs in our data between these models, then we will investigate further the pattern and magnitude of clustering effects to identify the cause of the differences.

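### Aim 6 relates operation-level compliance to SSI with a cohort intercept but no hospital term, so differences between paired hospitals can bias the OR in either direction

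*Combined protocol and SAP*

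**What the plan says.** SAP section 8.7 tests the theory of change by refitting the primary model with a different predictor: it will "build the same model as our primary analysis except to drop intervention status and replace it with the high compliance binary variable". The rest is inherited from sections 7.1 and 7.2:

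- a categorical month term with 18 levels;
- patient and procedure covariates: "The final list of eight fixed controls will be: age, hypertension, gestational diabetes, rupture timing, emergency vs. elective, wound classification, ASA classification, and indication";
- one clustering term: "The random effect for cohort will account for the within-cluster variance, assuming one shared ICC". The choice-of-model section (9.4) confirms this: "fitting random intercepts for each of the five cohorts, which are defined in tables 2 and 3 above".

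Neither hospital nor hospital type appears. Under Site randomization, the protocol sorts hospitals into a teaching/referral group and a regional/district/community group, then states: "One hospital in each group will be paired to create five clusters". As executed (SAP Table 2), cohort 1 has one hospital and cohorts 2 to 5 have two each.

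The flag is 5 or 6 domains against 0 to 4: "We based this cut point between 4 and 5 on the global distribution of compliance scores".

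The reading of the result depends on Aim 1. If Aim 1 succeeds, the SAP expects an OR below 1 of roughly similar significance. If Aim 1 fails, Aim 6 becomes an assay-sensitivity check, and a finding of no association is something "that will cast doubt on all the trial results and pose larger questions about measurement, data quality" and implementation.

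**The concern.** A cohort intercept fits Aim 1's exposure, because both hospitals in a cohort share one implementation date. It does not fit Aim 6. Compliance is a property of each operation, and its frequency can differ between two hospitals that share an intercept. If recorded SSI also differs between them, the flag partly stands in for hospital.

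The SAP itself expects hospitals to differ. Section 4.2 anticipates variation in control-period SSI rates, section 7.1 admits uncertainty about differences between hospitals, and the hospital sensitivity section (9.3) refers to culture and leadership. Differences in how completely infections were captured would act in the same way as differences in true risk.

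The stakes lie in the reading when Aim 1 fails. A spurious OR below 1 would give false reassurance about measurement, which is already in question after the audit. A masked association would wrongly discredit a sound null result.

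**Working it through.** Aim 6 has no stated sample size, power or effect, so there is no plan figure to reproduce.

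**Inputs from the documents.** Auditor follow-up by cohort, control plus intervention (SAP Table 4): 111+545=656; 422+851=1,273; 600+603=1,203; 783+607=1,390; 848+222=1,070. The total is 5,592. (Table 3 prints 5,525; the gap of 67 does not matter here.) These counts appear to include non-CS patients, so real intervals would be wider. About half of operations are high compliance. Expected mean SSI is 9% to 12%.

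**Assumptions not in the documents.** Even split of patients within each pair; cohort 1 uniform, with 50% high compliance and SSI midway between the two assumed rates; month and patient covariates omitted; hospital SSI and compliance rates as listed below.

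**One pair, no true association.** Let the hospitals have equal volume, high-compliance shares c1 and c2, and SSI risks r1 and r2.

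- Risk if high = (c1·r1 + c2·r2)/(c1 + c2)
- Risk if low = [(1−c1)·r1 + (1−c2)·r2]/(2 − c1 − c2)

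With shares 0.7 and 0.3 and risks 0.12 and 0.04:

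- High: 0.7×0.12 + 0.3×0.04 = 0.096
- Low: 0.3×0.12 + 0.7×0.04 = 0.064
- OR = (0.096/0.904)/(0.064/0.936) = 1.55, or 0.64 with the risks reversed

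**All five cohorts, true OR 1.00**, from expected counts in a logistic model. The first rate in each cell belongs to the same hospital of the pair.

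| High compliance | SSI | Direction across pairs | Cohort intercepts, OR (95% CI) | Hospital fixed intercepts, OR |
|---|---|---|---|---|
| 70/30% | 12/4% | all four aligned | 1.47 (1.21–1.79) | 1.00 |
| 70/30% | 4/12% | all four aligned | 0.68 (0.56–0.83) | 1.00 |
| 70/30% | 12/4% | three aligned, one reversed | 1.18–1.24, by which pair reverses | 1.00 |
| 70/30% | 12/4% | two aligned, two reversed | 0.97–1.03 | 1.00 |
| 70/30% | 14/6% | all four aligned | 1.37 (1.15–1.64) | 1.00 |
| 70/30% | 6/14% | all four aligned | 0.73 (0.61–0.87) | 1.00 |
| 60/40% | 12/8% | all four aligned | 1.08 (0.91–1.29) | 1.00 |
| 60/40% | 8/12% | all four aligned | 0.92 (0.78–1.10) | 1.00 |

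The 12/4% and 4/12% rows use fixed cohort intercepts. The others were fitted with a cohort random intercept, and fixed intercepts gave essentially the same values.

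**Masking, true within-hospital OR 0.65.** With 70/30% and 14/6%, the cohort model gives 0.90 (0.74–1.08). With 60/40% and 12/8%, it gives 0.70 (0.58–0.85). Hospital intercepts give 0.65 in both.

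**Hospital effects drawn independently** (400 simulations per setting, mean SSI 10%). With true OR 1.00, two-sided rejection under the cohort model is about 5%, 7.5%, 12.5% and 13% for logit SDs (SSI/compliance) of 0.3/0.5, 0.3/0.8, 0.5/0.5 and 0.5/0.8. In the last setting hospital intercepts bring it to about 5%. With true OR 0.65, power under the cohort model is at least 95% throughout.

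**Dropping the intervention term.** Take control SSI of 12%, a programme OR of 0.62 acting wholly outside compliance, and high compliance rising from 30% to 70%. On the Table 3 layout with cohort and month terms, the swapped OR is about 0.96 (0.79–1.15). With intervention kept it is 1.00. A rise from 20% to 90% gives about 0.89.

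**The case against.** The strongest reply is that the model does more than adjust for cohort. Month and eight covariates stay in, and urgency, wound class, ASA and indication could absorb part of a referral/district difference in risk. The illustrations omit them. No document gives SSI or compliance by hospital type. The one hospital below 3% is flagged in SAP section 4.2 as possible undercounting. The large ORs also need a wide SSI gap pointing the same way in every pair. All of this stands and limits the size. It does not remove the mechanism: patient covariates do not capture hospital practice or completeness of reporting, whereas a hospital intercept absorbs both.

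Three stronger readings might be inferred, and the documents do not support them.

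- *The flag breaks a protocol commitment or was tuned to the outcome.* The protocol's Analysis paragraph says "We will evaluate compliance individually and in an all-or-none manner", but that concerns compliance as an outcome. SAP section 5 labels Aim 6 as not pre-specified, and each domain is scored all-or-none. The cut came from compliance scores; nothing indicates that SSI results were used. The pilot also used a dichotomy, 3–6 against 0–2.
- *Removing the intervention term is a serious leak.* In the 30% to 70% illustration the OR moves only to about 0.96, well within its interval. The SAP makes the swap deliberately.
- *The trial's conclusion hangs on Aim 6.* SAP section 8.2 rests Aim 1 on its own OR and significance. The doubt-casting text applies only if Aim 1 fails and Aim 6 is null.

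Leave-one-hospital-out analysis is planned, but it is described for the main result and does not name Aim 6.

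**Conclusion.** The concern holds in a limited form. Aim 6 moves from a cohort-assigned exposure to a non-randomised one that varies within cohorts, without moving the adjustment down to hospital level. In the four two-hospital cohorts this can push the OR either way.

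The size is unknown, because hospital-level spread is not reported. Under the stated assumptions and no true association, the OR runs from about 1.0–1.1 (mild or mixed differences) to about 1.5 or its inverse (strong differences aligned in all pairs). Independent hospital effects give false-positive rates of about 5% to 13%. It would go too far to infer that the analysis is uninformative: with independent effects and a true OR of 0.65, power stays at 95% or more, and a real association is hidden only in the strongly aligned case.

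The primary conclusion is unaffected. This is a cheap improvement to an additional analysis, made worthwhile by the interpretive weight that section 8.7 gives it.

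**What to change.** In SAP section 8.7:

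1. Replace the cohort random intercept with hospital fixed effects in the Aim 6 model (nine hospitals), so that the OR is a within-hospital contrast.
2. Name Aim 6 in the leave-one-hospital-out analysis.
3. Describe the OR as an observational association between compliance and SSI.
4. Reword the reading for a failed Aim 1, so that a null Aim 6 is not used on its own as an assay-sensitivity test of the whole trial.

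Optional sensitivity analyses are to retain the intervention term, and to show the 0–6 score beside the 5–6 against 0–4 flag. The score assumes equal steps across unlike domains, so it complements the flag and need not replace it.

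The cost is a changed model line and some wording; hospital is already recorded. The interval widens slightly. In the 70/30%, 6/14% illustration the log-scale width goes from ln(0.87/0.61) = 0.355 to ln(1.21/0.83) = 0.377, about 6%.
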